| Outcome measures | Primary outcome measure:  Proportion of participants achieiving a gait speed of 0.4 m/s and 0.8 m/s. Gait speed will be measured during a 10 metre walk.  2.Time and number of steps to complete a 90 degree turn.  number of steps taken to turn and time taken to turn in addition to step widths and lengths during turning. The number of times participants fail to hit stepping targets when these are presented unpredictably in timing and location will be used to indicate the ability to adapt the straight gait pattern according to environmental demands.  Secondary outcome measures:  3.Timed up and Go (TUG) test.  4.Fugl-Meyer Assessment will be used to assess changes in motor and sensory impairment.  5.Berg Balance Scale  6.A scale to assess mobility of people living in the community after stroke in different settings:  8. Falls Efficacy Scale to assess changes in confidence in functional mobility tasks.  8.SF-12 . This is a short-form health survey with only 12 questions. It yields an 8-scale profile of functional health and well-being scores, including physical functioning, and social, emotional, mental and general health and has been included to measure effects on broader quality of life. |
| Statistical methods | This is a pilot study to determine answers to questions for the definitive trial so there will be no formal statistical testing. We will tabulate the number and percentage of patients who are invited to participate, and who are recruited, into each arm of the trial. We will also tabulate the % of therapists willing to recruit patients into each arm of the trial, and the percentage of patients with complete outcome data (with 95% confidence limits). We will also estimate the difference in proportions achieving the meaningful clinically important difference (with 95% confidence limits). |

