Visual deprivation is aimed at remedying deficits in central integration of sensory inputs (Smania et al, 2008) and an over reliance on visual information following stroke (Bonan et al, 2004). Such visual dependence has also been described in Parkinson’s Disease (PD) (Azulay et al, 2006). In contrast to the use of visual deprivation, PD literature points to the use of enhanced visual cues in order to overcome somatosensory impairments and improve gait characteristics. Many studies (e.g. Azulay et al, 2006) have reported improved symmetry and speed of gait in participants with PD following the use of horizontal line cues during the practice of walking exercises. It is thought that the benefits of these external visual cues are brought about by enhancing optic flow cues used in the control of locomotion and/or through directing attention to the process of improving aspects of quality of gait including stride lengths, symmetry of steps between legs, cadence etc (Azulay et al, 2006). Despite numerous small scale studies reporting the efficacy of using visual cues to enhance gait function, no RCTs have been published in the PD literature and this approach has not been explored in groups of participants with stroke.

Given that visual information comprises one of the most important and salient sources of information used during walking (Hollands et al. 2002; Patla 1997), that visual cues have been shown to be more effective than auditory cues in triggering gait adjustments (Bank et al, 2011), and that stroke survivors have been reported to become more dependent on visual cues (Bonan et al, 2004), we hypothesize that visual cues would be more effective in triggering gait recovery and adaptability following stroke than interventions not including visual cues. In the present study, we will integrate visual cues with walking and turning practice, and contrast this intervention to routine overground walking practice in order to test this hypothesis.

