## PRIMARY OBJECTIVE

Determine the numbers of patients willing to be recruited into both control and VCT groups

Determine the willingness of physiotherapists at each collaborating site to enrol patients to both control and VCT groups

Determine the numbers of patients who do not complete the allocated treatment, thus dropping out of the study, and determine the reasons for dropping out.

Use knowledge gathered about recruitment, outcomes and drop-out rates to determine sample size for a subsequent definitive trial.

Measure completeness of outcome data, i.e. percentage of patients with no missing values in outcome assessments.

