## SECONDARY OBJECTIVES

To gain preliminary evidence for the effects of task-specific locomotor practice incorporating visual cues compared to interventions not including visual cues on the ability to trigger gait recovery and adaptability following stroke.

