### Primary endpoint

To achieve the stated aims, we will: a) Determine the numbers of patients willing to be recruited into both control and VCT groups; b) Determine the willingness of physiotherapists at each collaborating site to enrol patients to both control and VCT groups; c) Determine the numbers of patients who do not complete the allocated treatment, thus dropping out of the study; d) determine the reasons for dropping out; e) Measure completeness of outcome data, i.e. percentage of patients with no missing values in outcome assessments. In order to measure completeness of outcome data, the primary and secondary outcome measures that we proposed to use in the future definitive trial will be carried out as follows :

Primary outcome measures for walking and adaptability of walking respectively:

1. *Proportion of participants achieiving a gait speed of 0.4 m/s and 0.8 m/s*. Gait speed will be measured during a 10 metre walk. Participants will be given a 3 meter warm-up distance and 3 metres to walk beyond the 10 metres, and will walk at their usual pace. The time taken to walk the 10 metres will be recorded. Perry et al ([1995](#_ENREF_35))have shown that these gait speed classifications correspond to walking abilities in the community, with a gait speed of < 0.4 m/s for household walkers, of 0.4 – 0.8 m/s for limited community walkers, and >0.8 m/s for community walkers. It has been demonstrated that progressing from one of these classifications to the next correlates with improvement in physical functioning and quality of life([Schmid, Duncan et al. 2007](#_ENREF_40)) and these categories also correspond with changes in the Functional Ambulation Category, a categorical scale, rating level of skill in functional ambulation([Holden, Gill et al. 1986](#_ENREF_21)).

2.*Measures of adaptability of gait*: Time and number of steps to complete a 90 degree turn & the number of failures to hit targets presented unpredictably in timing and location.

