## TRIAL / STUDY TREATMENT AND REGIMEN

The intervention groups under study are: (1) a specialized locomotor training program that includes use of visual cues (VCT) to improve temporal and spatial walking parameters and practice of turning ability as a rehabilitation modality provided on an outpatient basis and (2) a “usual” treatment package aimed at improving overground walking ability provided at outpatient rehabilitation clinics in the west midlands provided for stroke survivors.

The study is designed as a pilot RCT with the primary outcome being successful recovery of walking. Successful recovery of walking is defined as having achieved a 0.4 m/s gait speed or greater for persons with initial severe gait impairment (< 0.4 m/s), or as having achieved a 0.8 m/s gait speed or greater for persons with initial moderate gait impairment (≥ 0.4 m/s – < 0.8 m/s).

**Baseline assessments completed:** walking speed, time and steps taken for 90deg. Turn, Timed-up and Go, Fugl-Meyer Assessment, Berg Balance Scale, Functional Ambulation Classification, 6 minute walk test.

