**STATISTICS**

**METHODS**

### Statistical analysis

Demographic and other baseline data will be summarised by descriptive statistics (number[n], mean, standard deviation [SD], median, minimum and maximum) or frequency tables, stratified by treatment.

Measures of compliance will be summarised by descriptive statistics (number[n], mean, standard deviation [SD], median, minimum and maximum) or frequency tables, stratified by treatment.

Also calculation of the difference in proportions between the two treatments will be conducted to achieve meaningful clinically important difference.

No formal testing will be conducted since this is a pilot study to determine answers to questions for the definitive trial. Also no interim analysis will be conducted.

Further details of the statistical analysis will be supplied in the Statistical Analysis Plan (SAP), to be finalised in a seperate document.

All analysis will be performed using Stata 11, or above.

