### ASSESSMENT OF EFFICACY

No assessment of efficacy will be performed since this is a pilot study designed primarily for assessing the feasibility of conducting a larger study.

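### Feasibility is primary in the controlling sections, but stray wording makes walking recovery this pilot's primary outcome, and the analysis set then excludes people the feasibility endpoints must count

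*Protocol*

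**What the plan says.** **What is primary.** The Primary objective section opens with "Determine the numbers of patients willing to be recruited into both control and VCT groups" and continues with therapist willingness, drop-out, sample size for the next trial and completeness of outcome data. The Primary endpoint section repeats the feasibility items. It then explains why walking is measured at all: to measure completeness, "the primary and secondary outcome measures that we proposed to use in the future definitive trial will be carried out as follows".

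Three places lack that qualifier:
- Trial / Study Treatment and Regimen: "The study is designed as a pilot RCT with the primary outcome being successful recovery of walking". A definition follows, based on reaching 0.4 or 0.8 m/s according to initial severity.
- Synopsis, Outcome measures, under the primary label: "Proportion of participants achieiving a gait speed of 0.4 m/s and 0.8 m/s".
- Section 1.3, which proposes change in gait-speed class as the primary outcome measure.

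**Whether efficacy is assessed.** Assessment of efficacy: "No assessment of efficacy will be performed since this is a pilot study". Statistical analysis: "No formal testing will be conducted since this is a pilot study". Against these, the secondary objective is "To gain preliminary evidence for the effects of task-specific locomotor practice incorporating visual cues". Sections 1.1 and 1.4 say the present study will "contrast this intervention to routine overground walking practice in order to test this hypothesis". The Synopsis plans a between-arm difference in proportions with 95% confidence limits. The Statistical analysis section plans the difference but does not mention limits.

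**Who is analysed.** Definition of Population Analysed assigns both primary and secondary endpoints to a full analysis set. Membership requires a post-baseline assessment of the primary endpoint. One of the section's two descriptions of the set also requires at least one treatment.

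**The concern.** The protocol fixes the identity of the primary endpoint and the status of efficacy in ways that cannot all be followed. Both are protocol-level decisions, so a later analysis plan could not honour every statement without choosing between them.

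The consequence that changes a reported number is the analysis population. In a feasibility pilot, participants who leave early or miss assessments are part of the result. A set that admits only people with a post-baseline measurement removes some of them before drop-out and completeness are calculated. Those figures feed the definitive trial's design, so an optimistic completeness or drop-out rate would carry into its sample size.

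**Working it through.** **1. Primary endpoint.** Taking the Purpose, Primary objective, Primary endpoint and statistics sections together, feasibility is primary, and the walking measures are collected on behalf of the later trial. The treatment section's sentence is about this study and carries no such qualifier. Neither do the Synopsis entry or section 1.3. The intended meaning can be recovered, but the text conflicts.

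**2. Efficacy.** Three kinds of statement need separating.
- No formal testing, alongside an estimated difference with an interval: compatible.
- No assessment of efficacy at all, alongside a secondary objective of preliminary evidence and a planned between-arm difference: in conflict as worded.
- No formal testing and no efficacy assessment, alongside a statement that the present study tests the hypothesis: in conflict.

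**3. Analysis set.** The feasibility endpoints are recruitment, therapist willingness, drop-out and its reasons, and completeness. None has a post-baseline assessment in the sense the population definition needs, so the term there works only if it means gait speed. Yet the same section assigns all primary endpoints to that set.

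Let N be the number randomised, K those with no post-baseline gait measure, and C those with no missing outcome values. Anyone in K has missing outcome data, so none of K is in C.
- Completeness on all randomised: C / N.
- Completeness on the full analysis set as described without the treatment requirement: C / (N − K).

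The numerator is unchanged and the denominator falls, so completeness is overstated whenever K > 0 and C > 0. The protocol gives no expected K or C. Illustration with N = 60 (Synopsis; Randomization and Blinding) and assumed C = 42:

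| K (assumed) | C / N | C / (N − K) |
|---|---|---|
| 3 | 42/60 = 70.0% | 42/57 = 73.7% |
| 6 | 42/60 = 70.0% | 42/54 = 77.8% |
| 12 | 42/60 = 70.0% | 42/48 = 87.5% |

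Drop-out moves the other way. If 15 of 60 did not complete treatment and 6 of those had no post-baseline gait measure (assumed), 15/60 = 25.0% becomes 9/54 = 16.7%. Recruitment cannot be computed on this set at all, because its denominator is people approached, not people randomised.

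**4. Could walking recovery carry the primary role?** The protocol states no success rate, effect size or power, so there is no figure of its own to reproduce. The rates here are assumptions. The 95% half-width is 1.96 × √[p₁(1−p₁)/n₁ + p₂(1−p₂)/n₂].

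| Success rates | 20 v 20 |
|---|---|
| 20% v 20% | ±24.8 points |
| 20% v 40% | ±27.7 |
| 30% v 30% | ±28.4 |
| 30% v 50% | ±29.7 |
| 50% v 50% | ±31.0 |

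Power of a two-sided 5% Fisher test, by exact enumeration:

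| Control v VCT | 20 v 20 | 20 v 40 (VCT arms pooled) |
|---|---|---|
| 30% v 50% | 16.3% | 24.6% |
| 30% v 60% | 34.7% | 50.8% |

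The pooled column is shown because the Statistical analysis section refers to two treatments although three groups are randomised.

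**The case against.** The best defence is that the sections that govern design agree. Purpose, objectives, Primary endpoint and statistics all point to feasibility, and the Primary endpoint section says outright why walking is measured. On that view the treatment section repeats an outcome label, and sections 1.1 and 1.4 are background rationale rather than analysis instructions. The ban on efficacy assessment can be read as barring a conclusion rather than an estimate, in which case the outcome data needed to size the next trial are still produced. The power figures describe a test the protocol says it will not run.

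Much of this stands. A reader might infer two equally supported designs, or that the walking result decides whether VCT goes forward. The documents support neither: feasibility clearly predominates, and no section makes walking recovery a criterion for proceeding. A reader might also infer that a walking p-value is planned as the headline result. Both the Synopsis and the Statistical analysis section exclude formal testing.

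The defence does not reach the population definition. The qualifier in the Primary endpoint section does not change which participants enter the full analysis set, and the assignment of primary endpoints to that set is explicit. Nor does the qualifier alter the unqualified Synopsis entry or the literal breadth of the efficacy statement.

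**Conclusion.** The point holds as an inconsistency with one practical consequence. Feasibility is the intended primary endpoint, but the treatment section, the Synopsis and section 1.3 present walking recovery as primary without the qualifier. The efficacy statement, as worded, conflicts with the secondary objective, the planned difference in proportions and the hypothesis-test wording.

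The consequence is that drop-out and completeness, if analysed on the stated set, exclude people they must count. The direction for completeness is certain once anyone lacks a post-baseline gait measure. The size depends on how many do: about 4 to 18 percentage points in the illustration, for 3 to 12 such participants out of 60.

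The precision and power figures are context. They rest on assumed success rates of 20% to 60% and full follow-up of 20 per arm, or 40 v 20 if VCT is pooled. They show that the walking comparison cannot serve as a primary test, not that the protocol plans one. This should be corrected, but it does not undermine the trial.

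**What to change.** 1. In the Synopsis, section 1.3 and the treatment section, label recovery of walking as the primary clinical outcome proposed for the definitive trial. State that this pilot's primary endpoints are the feasibility measures in the Primary endpoint section.
2. Replace the Assessment of efficacy text with: *Clinical outcomes will be estimated by arm, with between-arm differences and 95% confidence limits, as exploratory; no conclusion on efficacy will be drawn.*
3. In sections 1.1 and 1.4, replace the statement that the study tests the hypothesis with one that it informs a definitive trial of it.
4. In Definition of Population Analysed, analyse drop-out and completeness on all randomised participants, and recruitment on all people approached. Define the full analysis set by a post-baseline gait-speed assessment and restrict it to the exploratory clinical outcomes.

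The cost is wording in about half a dozen places. No data collection, sample size or visit changes, and the sponsor gives up no efficacy claim that the no-testing statement had left open.

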**Randomisation**

**5-30day screening & consent:**

Self-selected gait speed, Star cancellation, Mini Mental Status Exam, Sheffield Screening for Acquired Language Disorders, modified Rankin Scale, Lesion location, Date of Stroke

**Potentially Eligible Participants Identified**

**Standard care: 1hr, 3X weekly for 8 weeks**

**VCT intervention: 1hr, 3X weekly for 8 weeks**

**Post-treatment assessment**

**Post-treatment assessment**

**Three month assessment**

**Three month assessment**

**Figure 1: Flow diagram of trial conduct**

**Visual Cue Training (VCT):**

Feasibility of VCT delivered in two ways will be examined. Both overground VCT and treadmill based VCT will share the same frequency, duration, intensity and progression as per below. Only the content of VCT will differ slightly between the two VCT arms and is detailed below.

Frequency: 2X/week, 8 weeks

Duration: 1hr,consisting of: warm up – 5 minutes, stretching – 5 minutes, Set up for training programme – 5 mins, training programme – 20-30 minutes overground walking practice (+ 10 minutes for rests as required) and cool-down - 5 mins

Intensity: The training program will begin with 5 minute bouts of walking with VCT interspersed with rests to total 20-30 minutes of walking practice. Once this is achieved, then the number of bouts may be decreased and the length of each bout increased. The target exercise capacity is 20 minutes of continuous, independent, good stepping. Good stepping is defined as walking with (1) an upright trunk with pelvic rotation to achieve limb loading, (2) symmetrical stride length, (3) symmetrical swing and stance time, (4) hip and knee flexion moments during swing initiation and swing, and (5) hip and knee extensor moments during stance and push-off with proper stance and swing kinematics.

In order to contrast intensity between VCT and UC groups a pedometer will be worn during training sessions to record the number of steps taken in each condition.

During the 20–30 minute training sessions the Borg scale Rate of Perceived Exertion will be monitored every 10 minutes initially to assure that the intensity of walking practice remains within acceptable limits. The American College of Sports Medicine criteria for terminating an in-patient exercise session are followed according to guidelines shown to be effective for persons post-stroke with multiple comorbidities([Rimmer 2000](#_ENREF_38)) and described in “stopping rules and discontinuation” above.

Goal setting and progression: Parametric training targets include: (1) gradually increasing walking speed in 10% increments, as tolerated, from baseline to the target threshold (either 0.4m/s or 0.8m/s depending on initial SSWS) (2) improving symmetry of gait in 10% increments, as tolerated (3) complete 90 degree turns within 2 seconds ([Thigpen, Light et al. 2000](#_ENREF_46)) and within 2 steps in either direction when cued unpredictably, (4) incremental decreases (by 10%) in the number of failures to hit targets when presented variably in time and space during straight walking (this targets adaptability of the straight walking pattern to be able to alter footplacement or speed as dictated by the visual cues and mimicks the adaptability of gait required in response to environmental demands).

In the first treatment phase, overall treatment aims for each session address improving speed and achieving symmetrical posture with spatial-temporal symmetry of the stepping pattern. For example, the participant may walk with a shorter step length for the non-paretic limb as a means to compensate for deficits in paretic limb and trunk control. The visual cues will be marked on the walkway to indicate the target of a 10% improvement in foot placement (overground VCT) and/or timing of foot placement (treadmill VCT) in the next step. In the first phase of treatment, each goal type (speed, symmetry) will be addressed individually in blocks of practice during each bout of walking. In this initial phase a decrease in gait speed may occur during the bout of practice in which gait symmetry is being targeted. Variation in other gait parameters will be allowed while practicing improvement in another parameter.

In the second phase of treatment practice of turning and adapting the gait pattern are layered into the treatment. The goal will be to improve foot placement during turning in 10% increments, as tolerated, towards the final goal of completing a turn in 2 steps and 2 seconds. Adaptability of foot placement during straight overground walking will be targeted by therpaists random verbal indications to avoid given targets as the participants walk across the floor. The goal will be to decrease the number of failures to avoid targets. Adaptability of foot placement during treadmill walking will be improved upon by decreasing the number of failures to avoid targets which are presented variably in time and space, by 10% increments as tolerated. Each goal type (speed, symmetry, turning and adaptability) will continue to be addressed individually in blocks of practice during each bout of walking such that the tasks are predictable and pre-planned. However, in this next phase of treatment participants will be asked to practice improving one aspect of gait e.g. symmetry, while maintaining new improvements in other aspects e.g. speed. In this way this phase of treatment we will aim to improve one aspect of gait at a time while constraining the other gait parameters to be maintained at newly improved levels.

The final phase of training continues repetitive practice of walking at increased speed with improved symmetry, but also provides opportunity for the participant to practice adapting the walking pattern *fully* according to environmental demands. This is achieved by unpredictable and randomized order of straight walking, turning and adaptable straight walking (the requirement to hit stepping targets with varying spatial and temporal properties).

Table 2: VCT treatment goal setting and progression.

| Progression | Treatment Goal Categories | | | | |
| --- | --- | --- | --- | --- | --- |
| Treatment Phase (sessions) | **Walking speed target** | **Symmetry target** | **Turning ability target** | **Gait adaptability/ translation to functional mobility** | **Intensity** |
| I (1-4) | increasing walking speed in 10% increments, as tolerated, from baseline to the target threshold (either 0.4m/s or 0.8m/s depending on initial SSWS) | improving symmetry of (a)step-length, (b) stance and swing phases in 10% increments, as tolerated |  |  | Four 5min bouts of walking to total 20mins of stepping with each bout addressing one of the goals at a time |
| II (5-10) | increasing walking speed in 10% increments, as tolerated, from baseline to the target threshold (either 0.4m/s or 0.8m/s depending on initial SSWS) | improving symmetry of step-length, stance and swing phases in 10% increments, as tolerated while maintaining new walking speed | 10% improvement in turning towards ability to turn in 2 steps, 2 seconds in either direction while maintaining new walking speed | 10% improvement in the number of failures to hit targets presented unpredictably in timing and location on both limbs while maintaining new walking speed | Increase bout duration and decrease number of bouts however each goal is still addressed individually in blocks of practice |
| III (11-16) | Practice at maintenance of walking speed over threshold and at altering speed as dictated by varying speed of presentation of footfall targets | Practice at maintenance of symmetrical stepping | 2 steps, 2 seconds in either direction when turns are unpredictable | Able to alter stepping pattern to hit targets presented unpredictably in timing and location on either limb | 20-30mins of sustained good quality stepping |

Goals will be reassessed weekly by assessing participants gait pattern and the goals adjusted as the target improvements are achieved. If the patient has achieved a gait pattern within normal limit values of stride length and gait speed for their age group [21], they will continue to practice adaptability targets at this level until the end of training. At the completion of each session goals for the next treatment session using the VCT modality are set, based on the performance.

Content: Both VCT interventions (overground and treadmill based) are designed to target the essential control and functional requirements of walking: (1) speed of walking, (2) a reciprocal stepping pattern, and (3) adaptability to behavioural goals of the participant and environmental constraints. The VCT interventions are designed to elicit step adjustments similar to that required in environments with clutter or situations requiring alterations to speed, foot-placement or direction using visual targets cueing spatial and/or temporal aspects of footfalls.

*Treadmill VCT:*

One treatment site will deliver VCT on a force-instrumented treadmill (CMill, Forcelink, NL) which uses assessment of each footfall to determine the timing and location of visual cues projected as light targets shone 2-3 steps ahead on the treadmill. stepping stones (dimensions: shoe length by 30cm in width) will be projected on the treadmill, such that the current and upcoming (approximately 2 steps ahead) stepping stones will be visible to the patient (Figure 1). The stepping stones will be presented to the left and right to cue spatial and temporal requirements of left and right footfalls, respectively. Custom-made software for presentation of visual cues contingent upon measures of the ongoing gait cycle will be used to control the temporal and spatial specifications of the stepping stones. For example, if steps on the paretic leg are shorter than the non-paretic side (as measured by the instrumented walkway patients are traversing) then the light control system will present the subsequent paretic leg stepping stone (i.e. the next stride or 2 steps ahead) at a distance 10% further than the previous step (in accordance with the goal to improve spatial symmetry by 10%). Stepping stones will appear at the time patients need to initiate stance phase on the subsequent step. Participants will aim to walk for 5 minute bouts of continuous walking as tolerated as above and aim to increase to 20 mins of continuous walking. .

*Overground VCT:*

In the sites delivering overground VCT, participants will walk over a carpet walkway marked with the outline of a grid. The visual cues will take the form of red target stickers placed into appropriate grid boxes to denote target footfall locations according to the goal for changes in step lengths and widths. Initially, an assessment of spatial parameters of overground gait will be required in order to determine required locations of targets on the walkway grid.

Initially, participants will walk at their self-selected speed for 5 mins. Gait parameters of the participant will be assessed using the GAITRite system (CIR Systems Inc.), including step length, stride length, velocity, temporal and spatial symmetry and cadence. This will determine the participant’s starting target step lengths and target timing of their steps during the subsequent visual cue training.

*Both Overground and Treadmill VCT:*

During practice of turning the target footfall locations will be outlined with tape on the floor throughout turns of 90 degrees in both directions in order to cue spatial aspects of stepping patterns during turning. The turning walkways will be at the half-way point in the straight 6m walkway. Such that patients will walk straight for 3 m, turn in the direction cued, by the therapist, and continue for 5m following the turn. The stepping stones will be located such that the leg contralateral to the turn is cued to step longer and wider, while the limb ipsilateral to the turn will have targets which are shorter and wider (in accordance with the limb on the outside of the turn needing to travel a greater distance through the arc of the turn ). Stepping targets during a turn will be located such that the turn can be achieved in the goal of 2 steps and 2 seconds – or in 10% increments towards this final goal.

During practice of adaptable straight walking stepping targets will appear with variable spatial and temporal locations on both the paretic and non-paretic sides and patients will be asked to avoid some targets. Targets to avoid will appear in different colours for the treadmill delivery of VCT and will be outliined in a different colour for the overground delivery of VCT. This mimicks the kind of adaptations to the straight gait pattern that might be required in uneven terrain or cluttered environments. The number of times patients fail to avoid a target will be used to measure adaptability.

In order to achieve the goal of improving adaptability of the gait pattern to behavioural goals of the participant and environmental constraints, in the final phase of treatment, turns will be practiced unpredictably with the therapist randomising order of straight walking with turns of 90degrees in either direction and straight walks with variable indications to avoid some targets.

